#### SHI study population

2.3.1

The SHI population for EvaClosure is selected from the data pool of a German statutory health insurance fund that comprises over 3 million insured persons. EvaClosure uses data from the years 2015 to 2021. Patients are selected if they
are 18 years or older, andhave a diagnosis code (of the 10th revision of the International Statistical Classification of Diseases and Related Health Problems; ICD-10) for AF documented in at least two different quarters during the baseline period (I48.0, I48.1, I48.2, I48.9)Patients are excluded from the sample in case of
discontinuous data coverage (e.g., due to interrupted insurance periods or change of health insurance fund)an absolute contraindication for ASA (an ICD-10 code for gastric or duodenal ulcers (K25.- or K26.-) or a prescription for methotrexate [Codes within the Anatomical Therapeutic Chemical Classification System (ATC): L01BA01 or L04AX03])previous heart transplant (code within the German Operation and Procedure Classification System; OPS: 5–375)malignant neoplasm of the heart, mediastinum, and pleura (ICD: C38.-) orpregnancy, birth, or postpartum diagnosis in the baseline period (ICD: O–.—)Patients are assigned to the high-risk group if in the baseline period they additionally have the following characteristics:
CHA_2_DS_2_VASc-Score ≥ 2, andhigh risk for bleeding, i.e., if at least one of the following criteria are met:
○HAS-BLED value of ≥ 3, or○an ICD-10 code for other non-traumatic intracranial hemorrhage (I62.-), or○gastrointestinal bleeding (K92.2), or○hematuria (R31), or○bleeding from the respiratory tract (R04.-), or○chronic kidney disease (N18.4)From the high-risk patients, the LAAC intervention group is selected using the following inclusion criteria:
Diagnosis-related group (DRG): F95A (interventional septal occlusion, age < 18 years, or atrial appendage occlusion) andOPS code 8-837.s0 (since 2016) or 8-837.s (before 2016)The control group (best medical care group) is also selected from the group of high-risk patients, defined by the following criteria:

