### Outcome measures and analyses

2.4

The EvaClosure study design consists of four modules that build on one another (see Table 2). For module A1, a cost-of-illness study assesses direct and indirect costs associated with a high risk of stroke and bleeding in patients with AF. Focusing on the high-risk group only, module A2 compares direct and indirect costs associated with LAAC treatment to best medical care. Module B1 quantifies the utility effect of LAAC in terms of QALYs gained compared with standard of care via data of the EvaClosure study population. The subsequent module B2, on the other hand, combines SHI claims data and data from the EvaClosure study population as well as CLOSURE-AF trial results to conduct a cost–utility analysis.

**Table 2 T2:** Overview study modules, design, and outcome measures.

Module	Main Objectives	Study population	Design	Time frame	Costs/Outcomes
A1	To assess cost of illness to high-risk of stroke and bleeding in patients with AF	SHI study population, divided into the high-risk AF group and the AF group without high risk	Longitudinal cohort study, retrospective (difference-in-differences)	2015–2021; 1 year before and 4 years after inclusion per individual	direct and indirect costs
A2	To assess direct and indirect costs of LAAC intervention vs. best available medical care in high-risk patients with AF	EvaClosure study population: high-risk AF patients divided into intervention and control groups as per the CLOSURE-AF protocol.	Longitudinal cohort study, prospective (difference-in-differences)	2018–2025; enrollment starting in 01/2021 with a follow-up of up to 24 months	Direct and indirect costs
		SHI study population: the high-risk AF group divided into intervention and control groups as close as possible to the CLOSURE-AF protocol	Longitudinal cohort study, retrospective (difference-in-differences)	2015–2021; 1 year before and 4 years after inclusion per individual	
B1	To assess the utility effect of LAAC compared with best medical care	EvaClosure study population: high-risk AF patients divided into intervention and control groups as per the CLOSURE-AF protocol	Longitudinal cohort study, prospective	2018–2025; CLOSURE-AF enrollment starting in 03/2018; obtaining informed consent for prospective and retrospective participation in EvaClosure started in 01/2021, patient individual follow-up of up to 24 months	Health-related quality of life, QALYs

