#### A1: resource utilization and cost of illness associated with high risk of stroke and bleeding in patients with AF

2.4.1

In the SHI patient database, ICD-10 diagnostic codes will be used to select high-risk AF patients from AF patients without high risk of bleeding and stroke for the cost analysis in module A1 (see section “SHI study population”). A patient's index quarter, regardless of later being allocated to the high-risk group or not, will be the quarter in which the SHI patient inclusion criteria are fulfilled for the first time in the pre-observation year. In addition to these criteria (also using ICD-10 diagnosis codes^6^), patients will be allocated to the high risk of bleeding and stroke group if they have a CHA_2_DS_2_VASc-Score ≥ 2 and one of the following: a HAS-BLED value of ≥3, a diagnostic code for other non-traumatic intracranial hemorrhage, gastrointestinal bleeding, hematuria, bleeding from the respiratory tract, or chronic kidney disease in the observation period. Applicable ICD-10 codes to assess these indications were selected in cooperation with the CLOSURE-AF investigators.

Hierarchically regularized entropy balancing (39, 40), a method for statistical matching, will be used to ensure similar characteristics in terms of age, gender, morbidity (Charlson comorbidity index), and healthcare costs between the high-risk group and the control group without the high risk at baseline.

The two patient groups will be descriptively characterized; location and dispersion measures will be compared with respect to the distribution of appropriate metric variables such as age, morbidity indices, and bleeding risk. Frequencies will be reported for ordinal variables. Differences in mean values for dependent variables, such as resource utilization and direct and indirect costs, will be analyzed by performing a bilateral significance test of independent samples depending on the specific variable distribution in the actual data. The analysis will be conducted by a difference-in-difference design, carried out as two-way fixed effects regression model, alleviating further unobserved structural differences between both groups that may remain after balancing.

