#### A2: direct and indirect costs in high-risk AF patients: LAAC procedure vs. best available medical care

2.4.2

To estimate direct and indirect costs, a population with maximum similarity to the EvaClosure study population will be selected from SHI claims data by statistical matching. Age, gender, comorbidity, CHA_2_DS_2_VASc and HAS-BLED scores, and medications (by classification) taken by control group patients will be used for matching of the populations, as observed by the quarter and year in which they and their statistical match meet the inclusion criteria. Matching will be verified using clinical trial data on medication, periprocedural events, (serious) adverse events, and comorbidities detected during follow-up visits of CLOSURE-AF trial patients. In the SHI population, healthcare costs of the LAAC group within a 2- and 5-year time frame will be estimated as the difference between the costs induced by the intervention group and the control group. Indirect costs will be evaluated based on the difference in the average length of incapacity to work documented per group, priced using industry-specific average employee compensation in Germany.

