Because patients are surveyed with the FIMA every six months, questions on resource utilization covering a period of 12 months (see above) were modified to cover a period of six months.Information on sociodemographic and socioeconomic data as well as on drug utilization is collected in the CLOSURE-AF study. Therefore, questions covering these topics (e.g., on sex, age, marital status, and drug utilization within the last seven days) were waived.To estimate the indirect costs, two questions on unemployability (i.e., duration within the last six months and profession) were added.Using descriptive statistics, measures of location and dispersion will be compared for similarity. Difference-in-differences estimation will be applied to evaluate the incremental costs of the LAAC procedure by comparing the costs of services incurred by the intervention group and the control group. The time frame covers five years, comparing the average costs of both groups before and after the quarter of LAAC or first treatment with one of the pharmaceuticals defined as best medical treatment in the study design section.

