## Discussion

3

According to available evidence, percutaneous catheter-based LAAC can be considered a potential effective alternative to medical therapies in stroke prevention for AF patients with a high risk of bleeding or contraindications to (N)OACs (50). In the United States, almost 40,000 LAAC procedures were included in the National Cardiovascular Data Registry LAA occlusion registry between 2016 and 2018, of which the majority were performed with favorable outcomes (51), and the European Society of Cardiology recommends considering the procedure for patients with contraindications to (N)OAC therapy in its current guidelines (21). However, distinct clinical superiority and economic benefits of this intervention over the best available drug therapy (standard care) still need to be confirmed, especially in patients at high risk of stroke and bleeding, as addressed by the CLOSURE-AF trial (23). As a health economic substudy, EvaClosure explores LAAC cost-effectiveness from both SHI and societal perspectives when directly compared with the standard drug therapy.

The results from clinical trials that—among other things—consider the occurrence of bleeding or stroke events as well as cardiovascular and all-cause mortality suggest that, for patients with AF, LAAC therapy is not inferior when compared with drug treatment (50). Therefore, we assume that the one-time LAAC procedure costs are compensated over time by the annual savings on drug therapy and fewer complications (e.g., reduced number and duration of inpatient stays due to stroke) (30, 50). The evidence suggests that risks of serious events are lower in LAAC-treated patients compared with the control group, thereby reducing disability and productivity loss in a medium-term time horizon of two years. In the long term (up to five years), we expect a less pronounced increase in outpatient costs, inpatient costs, and overall direct and indirect costs in LAAC–treated patients compared with the control group.

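### Module A2's claims difference-in-differences dates LAAC patients from the procedure but controls from first anticoagulant treatment, so drug costs are biased unless prior anticoagulant use is equal in both groups

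*Protocol article*

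**What the plan says.** Section 2.4.2 (A2) of the protocol article states: "Difference-in-differences estimation will be applied to evaluate the incremental costs of the LAAC procedure". The contrast is made by "comparing the average costs of both groups before and after the quarter of LAAC or first treatment with one of the pharmaceuticals" that make up best medical treatment. Table 2 gives the claims window as "2015–2021; 1 year before and 4 years after inclusion per individual".

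Section 2.3.1 defines the two claims groups. For LAAC: "From the high-risk patients, the LAAC intervention group is selected using the following inclusion criteria", after which come only a DRG and a procedure code. Controls are high-risk patients without LAAC who are treated with a NOAC or VKA. Neither definition sets a condition on earlier anticoagulant use, and no washout or new-user rule is given for controls.

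On matching, section 2.4.2 lists age, gender, comorbidity and the two risk scores, and adds that "medications (by classification) taken by control group patients will be used for matching of the populations". These variables are taken at the quarter in which inclusion criteria are met. Section 2.4.1 (A1), by contrast, also balances "healthcare costs between the high-risk group and the control group without the high risk at baseline".

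Section 2.4.2 also describes the cost result in another way: "healthcare costs of the LAAC group within a 2- and 5-year time frame will be estimated as the difference between the costs induced by" the two groups. Section 2.4.4 (B2) carries the A2 result into the ICER.

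**The concern.** Difference-in-differences needs the controls' change over time to stand in for the change that LAAC patients would have had without the procedure. If a control's clock starts at the first dispensing of an anticoagulant, the control change includes the cost of starting the drug. A LAAC patient who was already on such a drug would not have experienced that start. The estimator then credits LAAC with the drug the LAAC patient stops and also with the drug the control starts.

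This matters because the Discussion names "annual savings on drug therapy and fewer complications" as what is expected to offset the one-time procedure cost. The affected component is therefore central to the expected economic result. None of the sensitivity analyses in section 2.5 varies the index date.

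**Working it through.** The article states no cost figure for A2, so there is none to reproduce. The check is the algebra of a two-group before/after contrast, followed by a small simulation.

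**Inputs**
- c: annual anticoagulant cost. Not given; results are in units of c.
- s: share of LAAC patients on an anticoagulant in the pre-year and off it after the procedure. Not given; taken from 0 to 1. Section 1.1 says that a considerable proportion of high-bleeding-risk patients are undertreated or untreated, so s need not be large.
- q: share of controls on a listed drug in the pre-year. Zero if first treatment means initiation; otherwise not given.
- P: procedure cost spread over the post years.
- Window: one year before and four after (Table 2).

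**Algebra**
- LAAC change = P − s × c
- Control change = (1 − q) × c
- Difference-in-differences = P − (1 + s − q) × c
- Target contrast with best medical care = P − c
- Drug-cost bias = (q − s) × c per year

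The target assumes that, without LAAC, the LAAC patients would have used the drugs as controls do after index.

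| s | drug saving counted (q = 0) | bias per year (q = 0) | bias over 4 years (q = 0) | bias per year (q = 0.5) |
|---|---|---|---|---|
| 0 | 1.00c | 0 | 0 | +0.50c |
| 0.25 | 1.25c | −0.25c | −1c | +0.25c |
| 0.5 | 1.50c | −0.50c | −2c | 0 |
| 0.75 | 1.75c | −0.75c | −3c | −0.25c |
| 1 | 2.00c | −1.00c | −4c | −0.50c |

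Negative values make LAAC look cheaper than the target contrast.

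**Simulation check.** Settings: 2,000 patients per group, c = 1, a one-off procedure cost of 10 (10/4 = 2.5 per post year), s = 0.6, q = 0.
- Target: 2.5 − 1 = 1.50 per year.
- Algebra for the planned estimator: 2.5 − 1.6 × 1 = 0.90. The simulation returned 0.90.
- A post-index comparison alone returned 1.50.
- Shortfall: 1.50 − 0.90 = 0.60 = s × c.

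**Other costs.** Let hL and hC be transient acute costs in the pre-year of LAAC patients and controls. With q = 0 the net bias is −s × c − (hL − hC). At s = 0.5:
- hL = 1c, hC = 0: −0.5c − 1c = −1.5c
- hL = 0, hC = 1c: −0.5c + 1c = +0.5c, so LAAC looks dearer.

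**The case against.** The strongest reply is that the double count depends on one reading. No new-user rule is stated and section 2.3.2 guarantees only one baseline year, so first treatment could mean the first dispensing seen in the data. The drug bias could then have either sign, and at s = q = 0 it is nil. This stands, and it makes the size conditional. It does not rescue the design, because the bias vanishes only when q = s and nothing in the text brings that about.

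A second reply is that matching covers comorbidity and HAS-BLED, and is to be verified against trial data that include medication and adverse events. HAS-BLED may well capture bleeding risk. But the stated purpose is likeness to the trial sample, the only drug variable concerns controls, and no listed variable captures the timing or cost of a recent bleed. Figure 1, which is said to show matching criteria, could not be seen, so this rests on the text alone.

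Third, the between-group cost difference in the same section, read as a post-index comparison, would not double count. That is correct. But the same section and Table 2 name difference-in-differences, and the article does not say how the two relate.

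Fourth, controls may not persist on treatment: section 1.1 cites 15%–30% discontinuation or non-adherence in the first year. If only a share k of controls stay on the drug, the estimated drug effect is −(k + s − q) × c against a target of −k × c. The absolute bias is still (q − s) × c, but the factor (1 + s) no longer applies exactly.

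A reader might infer that LAAC is bound to look cheaper than it is in total. The documents do not support that: a bleed before LAAC pushes one way, but acute costs before a control's first anticoagulant push the other. Nor does the problem extend to the randomised EvaClosure arms, which can share the trial baseline as time zero.

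**Conclusion.** The point holds for the SHI claims comparison in A2. The index dates are not comparable, and the listed matching variables do not make prior anticoagulant use comparable either.

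If first treatment means initiation, the drug saving is counted (1 + s) times and LAAC drug cost is understated by s × c per year, or 4 × s × c over four post years. That factor assumes that controls stay on the drug and that treated LAAC patients stop it. Without the initiation reading, the drug-cost bias is (q − s) × c, of either sign. No euro amount can be given, since s, q and c are all absent, and the direction of the bias in total costs is not determined. Severity: should be fixed. A certain bias in favour of LAAC, or a defect that invalidates the ICER whatever the reading, would go beyond the text.

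**What to change.** - Give controls an index quarter comparable with the LAAC quarter. One way: for each LAAC quarter, draw high-risk AF patients without LAAC up to that quarter who start, continue or switch best medical care. A post-index comparison after adequate balancing is another acceptable route.
- Balance the LAAC and control groups on anticoagulant use, bleeding admissions and healthcare costs in the four pre-index quarters. A1 already balances baseline costs.
- State whether first treatment means initiation, with a washout, or first observed dispensing. Keep the first-treatment index as a sensitivity analysis.
- State whether the between-group cost difference or the difference-in-differences feeds the ICER.

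The cost is reprogramming on claims data that the study already uses; no new data are needed. A control may be eligible in several quarters, so standard errors must be clustered by patient if controls are reused.

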Although non-vitamin K antagonist oral anticoagulants (NOACs) substantially reduce the risk of stroke and systemic embolism in patients with AF, their use in patients with high bleeding risk may be limited by safety concerns and long-term treatment persistence. In pivotal phase III trials and subsequent meta-analyses, the annual rate of incidence of major bleeding during NOAC therapy ranged approximately from 2% to 4%, depending on patient risk profile and drug regimen, with gastrointestinal bleeding representing the most frequent severe bleeding manifestation (16–19). Furthermore, contemporary registry data indicate that persistence with oral anticoagulation declines progressively over time, with discontinuation or non-adherence rates of approximately 15%–30% within the first year of treatment and substantially higher cumulative discontinuation rates during longer follow-up times. The reported reasons include bleeding complications, perceived treatment burden, multimorbidity, drug–drug interactions, and patient preference (10, 20). Consequently, a considerable proportion of patients with AF and high bleeding risk remain undertreated or untreated in routine clinical practice. Current European Society of Cardiology guidelines therefore emphasize the need for individualized stroke prevention strategies and recommend a consideration of left atrial appendage closure in selected patients with contraindications to long-term anticoagulation (21).

Preliminary evidence suggests that percutaneous catheter-based left atrial appendage closure (LAAC) may represent an effective alternative for stroke prevention and may eliminate the need for permanent anticoagulation, especially for patients in this high-risk group (22). However, current research lacks a direct comparison of LAAC with NOAC therapy at a larger scale since this high-risk patient group is often not represented comprehensively in clinical studies. Therefore, additional evidence based on comparative studies is needed to recommend LAAC for routine clinical practice (23).

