#### SHI data collection

2.3.2

SHI patient data are transferred for each year for the time period from 01.01.2015 to 31.12.2021; for each patient included, at least one year of baseline data (used to confirm inclusion/exclusion criteria prior to observation period) and at least two years of follow-up data are captured. The data include information on
sociodemographic characteristics (age, gender, and insurance period)outpatient medical care [diagnoses (ICD-10), quarter of diagnoses, procedures, costs of care]pharmaceuticals (dispensed drugs, numbers of packages, prescription date, dispense date, and costs of therapy)medical devices and allied health services (type of therapy or device, service provider, and therapy duration and costs)unemployability (diagnoses, sick leave durations and payments, and durations), andinpatient medical care: main and secondary diagnoses (ICD-10) upon discharge, surgeries and procedures (OPS), date and cause of admission, date and reason for discharge, and DRG code.

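### The pre-period of the A2 claims difference-in-differences overlaps the window in which a bleed can qualify a patient, and neither bleed timing nor pre-index cost is named for balancing the two claims arms

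*Protocol article*

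**What the plan says.** Four parts of the protocol article bear on this.

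- **Selection (2.3.1, SHI study population).** "Patients are assigned to the high-risk group if in the baseline period they additionally have the following characteristics". Besides a CHA2DS2-VASc score of at least 2, one bleeding-risk criterion is enough. The list joins "HAS-BLED value of ≥ 3" to individual diagnosis codes by an *or*. Among these are non-traumatic intracranial haemorrhage, "gastrointestinal bleeding (K92.2), or" haematuria, respiratory-tract bleeding and one code for chronic kidney disease.
- **Baseline data (2.3.2, SHI data collection).** Each patient contributes "at least one year of baseline data (used to confirm inclusion/exclusion criteria prior to observation period").
- **Cost window and estimator (2.4, Table 2; 2.4.2).** For the A2 claims population Table 2 gives "2015–2021; 1 year before and 4 years after inclusion per individual" and names difference-in-differences. Section 2.4.2 describes this as "comparing the average costs of both groups before and after the quarter of LAAC or first treatment with one of the pharmaceuticals" that count as best medical treatment, over five years in total.
- **Matching (2.4.2 and 2.1).** Section 2.4.2 matches on "Age, gender, comorbidity, CHA_2_DS_2_VASc and HAS-BLED scores, and medications (by classification) taken by control group patients". Section 2.1 lists the trial data used for matching more broadly, including medical history, comorbidities and adverse events. Section 2.4.1 names baseline healthcare costs as a balancing variable, but for A1.

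Under section 2.4.4, the A2 result enters the incremental cost-effectiveness ratio (ICER) up to five years.

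**The concern.** Difference-in-differences removes stable differences between groups and shocks common to both. A bleed in the selection year need be neither. Its cost is largely transient, patients are in part selected because it happened, and it can be more frequent in one arm. The pre-period mean of the arm with more recent bleeds then lies above that arm's usual cost level. The excess is subtracted from every follow-up year, so the normal fall in cost after an acute event is read as a treatment effect.

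Because selection is by an *or* rule, two patients can both be high-risk although only one has just bled. The total HAS-BLED score does not record when a bleed took place or what it cost. The matching described brings claims patients close to trial patients; balance of the LAAC and control claims arms against each other on recent bleeding is not stated. At stake is the numerator of the two- and five-year ICER, where the error grows with each year counted.

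**Working it through.** The plan states no figure that could be reproduced, so the check is on the structure of the estimator.

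**Inputs from the article.** One pre-inclusion year and four years after (Table 2). Bleeding codes ascertained in the baseline period (2.3.1). Before-after comparison between arms (2.4.2).

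**Inputs the article does not give, hence assumed.** pL and pC are the shares of the LAAC and control claims arms with a costly bleed in the pre-year. C is the transient cost of such a bleed. Both arms have the same usual annual cost u, and LAAC has no true effect on cost.

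**Formula.**

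- Pre-year mean: LAAC u + pL x C; control u + pC x C.
- Each later year: u in both arms.
- Estimate per year = (post difference) - (pre difference) = 0 - (pL - pC) x C.
- Over k follow-up years: -k x (pL - pC) x C.

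**Illustrations (assumed values).**

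| pL | pC | C (EUR) | Per year | 2 years | 4 years |
|---|---|---|---|---|---|
| 30% | 30% | 10,000 | 0 | 0 | 0 |
| 35% | 30% | 5,000 | -250 | -500 | -1,000 |
| 40% | 20% | 10,000 | -2,000 | -4,000 | -8,000 |
| 50% | 20% | 10,000 | -3,000 | -6,000 | -12,000 |
| 20% | 40% | 10,000 | +2,000 | +4,000 | +8,000 |

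For the third row: -(0.40 - 0.20) x 10,000 = -2,000 per year; times 2 is -4,000 and times 4 is -8,000. A simulated quarterly panel (4 pre-quarters, 16 post-quarters, true effect zero) gave -1,947, -3,894 and -7,788 for that row, +16 per year for the first row and +2,001 per year for the last. This confirms the algebra only; it says nothing about the real shares or costs.

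**Recurrence.** Let r be the excess number of further bleeds per year in patients with a baseline bleed, at the same cost C. The post difference becomes (pL - pC) x r x C, and the estimate becomes -(pL - pC) x C x (1 - r). For r between 0 and 1 the error shrinks but keeps its sign.

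**Dropping the bleed quarter from the pre-period.** The pre difference becomes 0 while later bleeds still count, so the estimate becomes +(pL - pC) x r x C. The error changes sign instead of vanishing, so this cannot serve as the main rule.

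**If the estimator is a plain group difference.** Section 2.4.2 also describes the 2- and 5-year cost as the difference in costs between the groups. No baseline is then subtracted, and this particular error is absent.

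**The case against.** The case on the other side is substantial.

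- **A reader might infer that prior bleeding is unmatched.** The article does not support this. Section 2.1 lists medical history and adverse events for matching, section 2.4.2 lists comorbidity and HAS-BLED, and the figure that shows the matching criteria is not available here. The claims sample is also matched to a population randomised 1:1, so both arms share an intended target. What stands is narrower: neither passage names the timing of a bleed or pre-index cost.
- **A reader might infer that the error favours LAAC.** The argument would be that claims controls take a NOAC or VKA by definition, while the Background section says guidelines "recommend a consideration of left atrial appendage closure in selected patients with contraindications to long-term anticoagulation". That is a recommendation, not data on this fund's patients. Both arms must meet the same bleeding-risk rule, and controls are anchored at first drug treatment, which may itself follow a costly event. The direction is open.
- **A reader might take the overlap as complete.** Table 2 counts from inclusion, section 2.4.2 from the treatment quarter, and section 2.3.2 asks for at least one year of baseline. LAAC may come some time after qualification. For A1, section 2.4.1 even places the bleeding criteria in the observation period. The overlap follows from reading the sections together and may be partial for some patients.
- **The euro amounts are assumptions.** The qualifying codes include haematuria and respiratory-tract bleeding, and outpatient diagnoses are in the data, so many qualifying bleeds may be cheap.
- **The reach is limited.** Patient-reported resource use from the randomised arms will validate and supplement the claims costs, and the lifetime model uses state-dependent costs.

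Pre-trend displays and detailed covariate lists are often left to an analysis plan. Here, however, the article itself fixes the reference year and names cost balancing for A1 but not for A2.

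**Conclusion.** The point holds as a conditional one. On the windows stated, the A2 pre-period overlaps the period in which a coded bleed can qualify a patient, and the named matching variables do not secure equal recent bleeding or equal pre-index cost between the two claims arms. If those shares differ, the estimate is off by about -(pL - pC) x C per follow-up year, less in proportion to recurrence, and this accumulates in the ICER numerator up to five years.

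The conclusion assumes that difference-in-differences is the estimator, as Table 2 and the closing part of section 2.4.2 say, and that most of the bleed cost is transient. Neither the sign nor the size can be drawn from the article. The assumed range of EUR 500 to 6,000 over two years (EUR 1,000 to 12,000 over four) shows only that the issue merits a check. If the arms prove equal in recent bleeding, this error is nil.

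**What to change.** In section 2.4.2:

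1. Balance the LAAC and control claims arms on whether a listed bleeding code occurred before index, on its quarter relative to index, and on pre-index healthcare costs, as A1 does for baseline costs. Cost alone is not enough, because equal totals can combine a bleed in one arm with persistent costs in the other.
2. Report quarterly pre-index costs by arm as the check on parallel trends.
3. Use exclusion of the qualifying-bleed quarter only as a sensitivity analysis, for the reason shown in the working.
4. Reconcile the plain group difference with difference-in-differences as the A2 estimator, and inclusion with the treatment quarter as the index from which both windows run.

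The cost is wording and programming. Diagnosis quarters, admission dates and codes are already in the claims extract (2.3.2). The downside is somewhat more analysis work and possibly a smaller effective sample after balancing.
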